**10.3 Safety**

Adverse events will be collected from participating subjects. Reported adverse events will be adjudicated by the Data Safety Monitoring Board and analyzed per statistical plan.

Serious adverse events

Death, life threatening adverse event, inpatient hospitalization or prolongation of existing hospital stay, persistent or significant disability/incapacity, congenital anomaly/birth defect, medically significant event, including laboratory abnormalities.

**11. Sample size calculation**

Prior to this study, we recruited 28 subjects with refractory epilepsy to undergo PFO closure surgery and followed them up for one year after the operation. The primary efficacy outcome of this trial is the percentage decrease in the frequency of epileptic seizures during the first year after surgery compared to before surgery. In the 28 patients, the mean percentage decrease was 49.60%, with a standard deviation of 41.67%.

Combined with the control group parameter settings in drug research on refractory epilepsy treatment, we estimate that the surgical group's average therapeutic effect in this study is 50%, with a standard deviation of 0.42. The average percentage decrease in the control group, based on previous literature, is set at 20%, with a standard deviation of 0.20. Therefore, with a superiority margin of 0.1, a single-sided alpha of 0.025, and a test power of 0.80, the total sample size required is 88. To account for possible subject withdrawal and loss of follow-up, we increase the sample size required by 20%. Therefore, we plan to recruit approximately 110 subjects for this study.

12. **Statistical analysis**

1.Program of analysis set

The complete analysis plan consists of three sets: Full Analysis Set (FAS), Per-Protocol Analysis Set (PPS), and Safety Set (SS). Both FAS and SS will include all participants who are randomly assigned, but those with serious protocol violations, active withdrawal, serious adverse events, or extremely poor compliance will be excluded from PPS. For FAS, we intend to follow the modified intention-to-treat (mITT) analysis principles, which will exclude participants without a PFO diagnosis confirmed by intracardiac echocardiography during the surgical procedure.

2.Missing data

In the event that patients are lost to follow-up during the study, their corresponding data will be carried over and included in the analysis. The evaluation process will be performed by the project team's doctors, and the data will be reviewed by the data monitoring committee.

3.Statistical analysis methods

The demographic characteristics of PRE receiving PFO closure and those not receiving it will be compared to assess bias and ensure accurate representation of the participants. Primary and secondary outcomes will be described statistically using mean ± standard deviation, median, minimum, maximum, and other indicators. Categorical data will be described using frequencies and percentages.

The primary outcome of the trial will be analyzed using a mixed model of fixed and random effects, and factors with significant differences between the baseline datasets will be incorporated into the model as control variables. Additional analyses will include t-tests, chi-square tests, rank-sum tests, logistic regression, and propensity score matching to examine the secondary outcome indicators. Covariance analysis and mixed-effects models that consider the effect of time will be used to examine temporal trends in the clinical characteristics of epilepsy. All analyses will be performed using R-project version 4.2.1. Statistical significance will be set at two-sided p<0.05.

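### The trial is sized to beat control by more than a 10-point margin, but the stated significance rule carries no margin, so the success criterion and the 80% power belong to different hypotheses

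*Protocol*

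**What the plan says.** The sample size section (Section 11) gives these assumptions for the percentage reduction in seizure frequency:

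- Closure arm: "we estimate that the surgical group's average therapeutic effect in this study is 50%, with a standard deviation of 0.42".
- Control arm: "The average percentage decrease in the control group, based on previous literature, is set at 20%, with a standard deviation of 0.20".
- Hypothesis and result: "with a superiority margin of 0.1, a single-sided alpha of 0.025, and a test power of 0.80, the total sample size required is 88".

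The total is then raised to about 110 for withdrawal and loss to follow-up.

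Section 12, under statistical analysis methods, says that the primary outcome will be analysed with a mixed model, adjusted for baseline factors that differ significantly. The paragraph ends with the rule for significance: "Statistical significance will be set at two-sided p<0.05". It gives no margin, no shifted null hypothesis and no confidence-limit criterion. Section 4 says only that the trial is a 1:1 superiority trial. The margin appears nowhere outside Section 11.

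**The concern.** Section 11 implies the null hypothesis that closure minus control is at most 0.10, tested one-sided at 0.025. A plain two-sided p-value below 0.05 from a treatment effect in a model tests the null hypothesis that the difference is zero. The same data can reject one and not the other.

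Two things are at stake. First, the power quoted to justify the trial's size is not the power of the test that the analysis section states. Second, a result could be reported as positive while failing the hypothesis for which the trial was sized. Because the protocol does not say which standard governs the primary claim, that choice could be made after the results are known. The trial is open-label and the intervention is a permanent implant, so the standard of proof should be fixed in advance.

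**Working it through.** **Inputs (all from Section 11, with 1:1 allocation from Section 4).** Means 0.50 and 0.20, so the assumed difference is 0.30. Standard deviations 0.42 and 0.20. Margin 0.10. One-sided alpha 0.025. Power 0.80. The sum of the variances is 0.42² + 0.20² = 0.1764 + 0.0400 = 0.2164.

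**1. Reproducing 88.** With the margin, the effective difference is 0.30 − 0.10 = 0.20.

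n per arm = (1.960 + 0.842)² × 0.2164 / 0.20² = 42.5, so 43 per arm by the normal approximation (86 in total).

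With a Welch t-test, power is 0.792 at 43 per arm and 0.802 at 44. That gives 44 per arm, or 88 in total, as stated. The dropout step also reproduces: 88 / (1 − 0.20) = 110.

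**2. The same calculation without the margin.** The effective difference is 0.30 at two-sided 0.05.

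n per arm = (1.960 + 0.842)² × 0.2164 / 0.30² = 18.9, so 19 per arm by the normal approximation.

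The Welch t-test needs 21 per arm (power 0.815), or 42 in total. The margin therefore accounts for more than half of the 88 patients. At 44 per arm the power of the zero-difference test is 0.988.

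**3. Where the two rules disagree.** At 44 per arm the standard error is √(0.2164 / 44) = 0.0701, and the Welch critical value is about 2.00.

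- Against zero: the observed difference must exceed 2.00 × 0.0701 = 0.140.
- Against the margin: it must exceed 0.10 + 0.140 = 0.240.

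Observed differences from about 14 to 24 points are significant under Section 12 and fail under Section 11. At 55 per arm the standard error is 0.0627 and the range is about 12.5 to 22.5 points.

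**4. How often this would happen (Welch, 44 per arm).**

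| True difference | Met: p<0.05 against zero | Met: margin test | Falls between |
|---|---|---|---|
| 10 points | 28.9% | 2.5% | 26.4% |
| 20 points | 80.2% | 28.9% | 51.3% |
| 30 points | 98.8% | 80.2% | 18.6% |

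With 55 per arm and a true difference of 10 points, the zero-difference test is met 35.0% of the time and the margin test still 2.5%.

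**5. The alpha levels are not the problem.** One-sided 0.025 and two-sided 0.05 share the same critical value in the favourable direction. The only mismatch is the margin.

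**The case against.** The strongest reply is that Section 12 is silent on the margin and does not reject it. The sentence on significance closes a paragraph that covers all the analyses and may be meant only as a general significance level. A two-sided 5% level is compatible with a margin test read from a 95% confidence interval, and a statistical analysis plan that is not at hand might apply the margin in that way. This stands to the extent that the zero null is the ordinary reading of Section 12 and not its express wording. It does not remove the conflict. The protocol states a decision rule, and followed as written that rule does not test the hypothesis set out one section earlier. A later plan that applied the margin would still leave the two sections to be reconciled.

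A second point also has force. The 29% is not a false-positive rate for the zero-difference test. If closure truly beats control by 10 points, concluding that it is better than nothing is correct, and that test keeps its own one-sided error of 2.5%. The 29% is an error only if the margin is meant to govern the claim, and that is what the protocol leaves open.

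Third, under the zero-difference reading the trial is generously sized and not underpowered. That is true. It limits the harm to an unclear claim and a misattributed power, and does not make the analysis itself invalid.

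**Conclusion.** The point holds. The figure of 88 is arithmetically sound, but it belongs to a margin hypothesis that the analysis section does not carry forward. The quoted 80% power is not the power of the stated test, which is about 99% under the same assumptions. The two rules disagree for observed differences of about 14 to 24 points. Even if the sponsor's assumed 30-point effect is true, about 19% of trials would land in that range.

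These figures rest on the planning standard deviations, 44 evaluable patients per arm and an unadjusted comparison of means. The adjusted mixed model could move the cut-offs but cannot reconcile a null of 0 with a null of 0.10. Because this concerns the success criterion for the primary outcome, it must be settled before the data are analysed.

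**What to change.** Choose one hypothesis and state it in both sections.

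- **If the margin governs:** add to Section 12 that primary success requires the lower limit of the two-sided 95% confidence interval for closure minus control, in mean percentage reduction, to exceed 10 points. This is the one-sided 0.025 test of Section 11. Report the test against zero as supportive only. Section 11 then stands unchanged.
- **If the margin does not govern:** delete it from Section 11 and restate the power of the zero-difference test at 88 evaluable patients as about 99% under the same means and standard deviations.

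Either change costs about a sentence in the protocol, repeated in the analysis plan, with no extra patients or visits. Keeping the margin makes success harder to reach, but the sample size has already allowed for that.

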**8. Discontinuation criteria**

1.Serious adverse events occurred during the trail, such as severe cardiovascular and cerebrovascular emergencies, seizures with cardiac arrest, status epilepticus, or other symptoms of serious mental illness.

2.Adverse events occurred during the trail, including allergy to antiplatelet drugs or intolerable side effects, etc.

3.Participants with incomplete data or serious violation of the protocol.

For subjects who are lost to follow-up, attempts to contact the subject will be documented on a Discontinuation CRF. If the subject fails to comply with at least one follow-up visit, the study center must make attempts to contact the subject. There must be at least three attempts to contact the subject, which includes one attempt via registered mail. Details of the attempts must be documented in the subject’s chart.

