2. Anticipated Adverse Events: adverse events will be classified as either serious adverse events, adverse events or other events and will be identified as either device related, procedure related or “other” (such as pre-existing conditions).

Device failures would include but are not limited to: device removal (due to embolization or misplacement), thrombus formation on the device surface with the risk of subsequent embolization, infectious endocarditis, device collapse due to structural failure, and cardiac perforation due to the presence of the device.

The DSMB met to develop the adverse event definitions. All reported adverse events will be evaluated and categorized as either Serious Adverse Event, Adverse Event, or Other Event based on the following definitions. The DSMB will have the final rule on all adverse events categorizations.

a. Serious Adverse Events

Death, life threatening adverse event, inpatient hospitalization or prolongation of existing hospital stay, persistent or significant disability/incapacity, congenital anomaly/birth defect, and medically significant event, including laboratory abnormalities.

b. Adverse Events

Any reported adverse event not categorized as serious adverse events or other events. Adverse events are defined as an undesirable health occurrence or untoward deviation in health away from baseline, whether or not device or procedure related.

c. Other events

Reported events deemed not to be adverse events by the DSMB. These events may be changes from baseline but not untoward medical occurrences.

The DSMB further defined the following Anticipated Adverse Events. The above mentioned definitions will be applied to the following events to categorize severity. Strong consideration will be given in the determination of procedure or device related for events occurring within 30 days of the procedure. These potential events include, but are not limited to:

Anticipated Adverse Events

Air embolus – symptomatic event resulting from introduction of air into circulatory system

Allergic dye reaction – idiosyncratic reaction to dye used in imaging

Allergic drug reaction – idiosyncratic reaction to drugs used

Anesthesia reactions – idiosyncratic reaction to anesthetic agent used

Apnea – cessation of breathing

Arrhythmia – cardiac rhythm disturbance

Bacterial endocarditis – documented infection of vascular structures including cardiac and related blood vessels

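### The per-protocol set drops every participant with a serious adverse event, so it is selected on post-randomisation outcome and its contrast can be biased, in a direction and size the protocol does not fix

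*Protocol*

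**What the plan says.** Section 12, item 1, names three analysis sets. For the full analysis set (FAS) and the safety set (SS) it says: "Both FAS and SS will include all participants who are randomly assigned". It then narrows the FAS to a modified intention-to-treat set, "which will exclude participants without a PFO diagnosis confirmed by intracardiac echocardiography during the surgical procedure", a restriction that has nothing to do with adverse events. For the PPS it lists four separate grounds for removal: "but those with serious protocol violations, active withdrawal, serious adverse events, or extremely poor compliance will be excluded from PPS". The serious-adverse-event ground carries no limit by cause, by timing or by effect on adherence.

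Three other sections determine who this catches:

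- Section 10.3 defines a serious adverse event broadly, starting with "Death, life threatening adverse event, inpatient hospitalization or prolongation of existing hospital stay, persistent or significant disability/incapacity".
- Section 8 gives examples, "such as severe cardiovascular and cerebrovascular emergencies, seizures with cardiac arrest, status epilepticus, or other symptoms of serious mental illness", and makes serious adverse events the first of its discontinuation criteria.
- Section 9 lists device failures, among them "device removal (due to embolization or misplacement), thrombus formation on the device surface with the risk of subsequent embolization, infectious endocarditis".

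The primary outcome in section 10.1 is the percentage reduction in seizure frequency over the first year. Its postoperative value requires valid diaries for more than 95% of follow-up. Adverse event incidence is itself a secondary outcome in section 10.2. Section 12 does not say which analysis set is primary.

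**The concern.** A per-protocol set is meant to show the effect in participants who were treated and observed as planned. A serious adverse event is not a departure from the plan. It is something that happens to the participant after randomisation, and in this trial it can be linked to the result in two ways.

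First, it overlaps with the outcome. Status epilepticus is a seizure outcome, and an admission for worsening seizures meets the section 10.3 definition. Such a participant leaves the PPS because the disease being measured got worse.

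Second, exposure differs by arm. Only the closure arm has an implant, so only it can have the device failures in section 9. That arm also has a hospital stay for the procedure (section 6.4) that a complication could prolong.

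What is at stake is how the PPS can be read beside the FAS. If the two differ, or agree, part of the reason may be the removal of harmed participants and not adherence.

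**Working it through.** **The plan's own figures, for scale.** Section 11 gives means of 50% and 20%, SDs of 0.42 and 0.20, a margin of 0.10, one-sided alpha of 0.025 and power of 0.80.

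- Normal approximation: n per arm = (0.42² + 0.20²)(1.960 + 0.842)² / (0.30 − 0.10)² = 42.46, so 43 per arm and 86 in total.
- With the t distribution (Welch degrees of freedom), power is 0.792 at 43 per arm and 0.8015 at 44, which gives the stated 88.
- 88 / (1 − 0.20) = 110, as stated.

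The sample size therefore reproduces and is not in question. The useful yardsticks are the planned difference of 30 points and the margin of 10 points.

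**Effect of the exclusion rule.** In one arm, let p be the proportion with a serious adverse event, m the mean percentage reduction in the others, and g the number of points by which those with an event do worse.

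- Mean with everyone kept: (1 − p)m + p(m − g) = m − pg.
- Mean after exclusion: m.
- Exclusion raises the arm mean by pg.

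For closure (T) minus control (C), the PPS contrast shifts by **pT·gT − pC·gC**.

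**Numbers.** The protocol gives neither p nor g, so all inputs in this table are assumptions.

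| pT | pC | gT (points) | gC (points) | Shift (points) |
|---|---|---|---|---|
| any | any | 0 | 0 | 0 |
| 5% | 5% | 50 | 50 | 2.5 − 2.5 = 0 |
| 10% | 5% | 50 | 50 | 5.0 − 2.5 = +2.5 |
| 15% | 5% | 50 | 50 | 7.5 − 2.5 = +5.0 |
| 15% | 5% | 50 | 25 | 7.5 − 1.25 = +6.25 |
| 10% | 10% | 50 | 25 | 5.0 − 2.5 = +2.5 |
| 5% | 10% | 50 | 50 | 2.5 − 5.0 = −2.5 |

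A positive shift favours closure. The range over the scenarios computed is −2.5 to +6.25 points. These are not the extreme corners of the assumed ranges. If one arm's gap is 50 points and the other's is zero, the limits are 0.15 × 50 = +7.5 and −(0.10 × 50) = −5 points.

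**Does the rule only repeat non-adherence?** Withdrawal, serious violation and very poor compliance are already separate grounds in section 12, so the serious-adverse-event ground adds only people not caught by those three. One such group is identifiable. Assigned antiplatelet treatment ends at 24 weeks while follow-up runs to 48 (section 5.1). A participant who completed treatment as assigned and had a serious adverse event at week 40 would still be removed.

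**The case against.** The strongest defence is section 8. Serious adverse events are a discontinuation criterion there, so a participant with one may not complete the 24-week regimen or the 48-week follow-up. On that view section 12 merely carries discontinuation into the PPS. This does not rescue the rule, because section 12 excludes on the event and not on stopping, and it catches events after treatment is complete. The defence does show that editing section 12 alone may restore few people. A participant discontinued early could also miss the 95% diary requirement and drop out by that route.

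Four stronger readings are tempting, and the protocol does not support them.

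- A reader might infer that the PPS must favour closure. The selection mechanism is fixed by the wording, but the direction is not. More seizure admissions among controls would push the contrast the other way, and balanced arms would give no shift.
- A reader might infer a large bias by supposing that affected closure participants' seizures double (−100%) while the rest improve by 50%. That is a gap of 150 points, about 3.6 of the protocol's SDs of 42 points. At a 5% event rate it moves the closure mean by 0.05 × 150 = 7.5 points. Nothing in the protocol supports such a gap. The figure also has no control-arm term, so it should not be set against a between-arm margin.
- A reader might infer that the main result is compromised or harms are hidden. This rule leaves these participants in the FAS and SS, and adverse event incidence is a listed outcome.
- A reader might infer that the sponsor will rely on agreement between FAS and PPS. The protocol states no such use.

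It is also true that any per-protocol set selects after randomisation. The difference here is that the selecting variable can be the outcome itself, with no departure from the plan.

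**Conclusion.** The concern holds for the PPS. As written, section 12 removes participants because of a post-randomisation event that can be a seizure outcome or a harm of the tested procedure, even when they followed the protocol. The PPS contrast can therefore be biased. Its direction and size cannot be derived, because the protocol gives no event rates and no outcome gap. The range of −2.5 to about +6 points rests wholly on the assumed rates and gaps, and the shift is zero if events are unrelated to seizure change or the arms balance. Sections 8 and 9 make exact balance hard to count on. The effect is modest beside a planned difference of 30 points, but not negligible beside a margin of 10. The FAS, the SS and the sample size are unaffected by this rule. It is worth correcting because the wording is explicit and the correction is simple.

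**What to change.** In section 12, item 1, delete serious adverse events from the grounds for leaving the PPS. Define the set by major protocol deviations and adherence to the assigned intervention only, and state that a participant with a serious adverse event who otherwise meets that definition stays in.

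Reconcile this wording with section 8, which lists serious adverse events as a discontinuation criterion, and with the 95% diary requirement in section 10.1. The protocol should make clear how a participant with such an event is counted under each, so that the same people are not removed indirectly. This concerns how participants enter the analysis and does not ask for any change in how they are managed.

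The cost is a short wording change in section 12 and cross-checks with two other sections. The sample size of 88, or 110 with dropout, stays as it is. The downside is that the PPS result, normally read as supportive, may look slightly less favourable.

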**6. Interventions**

**6.1 Intervention grouping**

Participants in the PFOC-RE trial will be randomly assigned to either the surgical intervention group or the control group. The surgical intervention group will undergo PFO closure surgery and receive antiplatelet therapy for six months. This therapy will include 75mg of clopidogrel and 100mg of aspirin daily for the first three months. From the fourth to the sixth month, the participants will switch to taking 100mg of aspirin daily. Meanwhile, the control group will not receive PFO closure surgery but will still need to undergo antiplatelet therapy for six months with the same medication regimen as the surgical intervention group.

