**6.2 Baseline Evaluation**

Baseline protocol-required testing as part of this study are:

- Medical history and risk factors
- Neurology evaluation
- Electrocardiogram (ECG) or Holter study
- Transesophageal echocardiography (TEE) with bubble study
- Magnetic resonance imaging (MRI) or Cat scan (CT)
- Magnetic resonance angiography (MRA), duplex sonography, CT angiography or contrast angiography.

- MRA uses magnetic radio wave energy to look at blood vessels in the body

- Duplex sonography uses high frequency sound waves (Doppler ultrasound) to

measure the size and blood flow through a blood vessel

- CT angiography or contrast angiography uses X-rays and injection of intravenous contrast medium to see the blood flow in the arterial vessel throughout the body

- Pregnancy test (for women of child-bearing potential)
- Blood tests (approximately 4-5 teaspoons or 20-25 ml)

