**6.4 Intervention description**

The PFO occluder is a self-expandable, double disc device made from a wire mesh. The two discs are linked together by a short connecting waist. The discs have fabric sewn into them. The fabric used in the device is the same as that used by surgeons to close other cardiac defects. The PFO occluder will remain implanted in patients heart.

Subjects will have the PFO occluder procedure in the cardiac catheterization laboratory, or “cath lab.” Local or general anesthesia will be used and there should not be significant discomfort. This is a non-surgical procedure done using X-ray guidance in which a catheter is inserted through a blood vessel in your thigh up into subjects heart. A catheter is a sterile, flexible, hollow tube that is inserted into a blood vessel to allow for injection or removal of fluids or to pass devices through. After the procedure, subjects may experience some discomfort in the area where the catheter was inserted.

To help doctor evaluate subjects PFO during the procedure, subjects will have a Transesophageal Echocardiography (TEE), angiography and/or maybe intracardiac echocardiography (ICE) done. TEE is an ultrasound test to see subjects’ heart, where an imaging probe is placed through mouth into esophagus (swallowing tube). Some soreness may persist in esophagus for about one week. Angiography is an X-ray of blood vessels or heart chambers filled with a contrast dye that allows doctor to see moving pictures of heart. During angiography, a catheter is passed through a blood vessel in thigh up into heart. If doctor decides to look at heart using ICE, doctors will pass an ICE imaging probe through a blood vessel in thigh up into heart.

After doctor has measured PFO, an PFO occluder is passed through the catheter and positioned in the middle of left atrium. The left disk is deployed, and then drawn against the atrial septum. The right disc is then deployed. After doctor is satisfied with the position of the device, it is released from the delivery cable using a screw mechanism.

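### The full analysis set drops participants on an intra-procedural echo check that only the closure arm can have, so no stated efficacy set keeps the randomised comparison

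*Protocol*

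**What the plan says.** Protocol Section 12 (Statistical analysis), item 1, names three sets: the FAS, the per-protocol set (PPS) and the safety set (SS). It first states that "Both FAS and SS will include all participants who are randomly assigned". It then says that the FAS follows modified intention-to-treat principles, "which will exclude participants without a PFO diagnosis confirmed by intracardiac echocardiography during the surgical procedure". For the PPS it says that "those with serious protocol violations, active withdrawal, serious adverse events, or extremely poor compliance will be excluded from PPS". No set is named as primary for efficacy.

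Section 6.1 states that "the control group will not receive PFO closure surgery but will still need to undergo antiplatelet therapy for six months". Section 6.4 describes imaging during the closure procedure: "subjects will have a Transesophageal Echocardiography (TEE), angiography and/or maybe intracardiac echocardiography (ICE) done". It adds that intracardiac echo is done if the doctor decides on it.

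PFO status is also assessed before allocation, in both arms. Inclusion criterion 3 (Section 5.2) requires a right-to-left shunt of at least grade 2 on contrast transthoracic echo. Section 6.2 lists "Transesophageal echocardiography (TEE) with bubble study" as required baseline testing. Section 7 places randomisation after the baseline examination, and the device procedure within 21 days after randomisation.

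**The concern.** The FAS is described as everyone randomised and, in the same paragraph, as everyone randomised minus those who fail a check. That check is made after randomisation, during a procedure given to one arm only. Suppose two patients have the same misleading screening echo. The one allocated to closure can be removed when the intracardiac echo does not confirm the PFO. The one allocated to control has no such examination and stays. The arms being compared are then no longer the groups that were randomised.

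Two features add to this. The intracardiac echo is optional, so membership of the FAS may depend on an operator's imaging choice as well as on the patient's anatomy. The trial is also open-label with an unblinded surgeon (Sections 4 and 7), so the person doing the imaging knows the allocation.

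The PPS offers no way out, because withdrawal, compliance and serious adverse events all arise after randomisation. What is at stake is whether the efficacy estimate can be read as the effect of random assignment to closure.

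**Working it through.** **1. The rules side by side.**

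| Question | Closure arm | Control arm |
|---|---|---|
| PFO assessed before randomisation (5.2, 6.2, 7) | Yes | Yes |
| Procedure performed (6.1) | Yes | No |
| Intracardiac echo possible (6.4) | Yes, optional | No |
| Can leave the FAS for an unconfirmed PFO (12) | Yes | No |

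Nothing elsewhere in the protocol gives controls an equivalent confirmation step or limits the FAS rule to information available before randomisation. The rule also does not say whether a closure patient who had no intracardiac echo, or never reached the procedure, counts as unconfirmed.

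**2. The plan's own figures (Section 11).** Closure mean 50%, SD 0.42; control mean 20%, SD 0.20; margin 0.10; one-sided alpha 0.025; power 0.80.
- Difference beyond the margin: 0.50 − 0.20 − 0.10 = 0.20.
- Normal approximation: n per arm = (0.42² + 0.20²)(1.960 + 0.842)² / 0.20² = 42.5, so 43 per arm and 86 in total.
- With the t distribution: 44 per arm, 88 in total, as stated.
- Allowing for 20% loss: 88 / (1 − 0.20) = 110, as stated.

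The sample size reproduces and is not in dispute.

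**3. Illustration A: confirmed patients average 50%, unconfirmed patients 20%, controls 20%.** The unconfirmed share f is assumed; the documents give none. With about 55 per arm, 5% is 2.75 patients and 10% is 5.5.
- f = 5%: all-randomised closure mean = 0.95 × 50 + 0.05 × 20 = 48.5; difference = 48.5 − 20 = 28.5 points.
- f = 10%: 0.90 × 50 + 0.10 × 20 = 47.0; difference = 27.0 points.
- After the exclusion: 50 − 20 = 30 points in both cases.

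The gap is 1.5 to 3.0 points. The standard error at 44 per arm is √((0.42² + 0.20²)/44) = 7.0 points, so the gap is about 0.2 to 0.4 standard errors.

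**4. Illustration B: the all-randomised closure mean is held at 50%.** Retained mean = (50 − f × m)/(1 − f), where m is the mean of those excluded. The true all-randomised difference is 30 points.

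| f (assumed) | Difference after exclusion, m = 20 | Difference after exclusion, m = 0 |
|---|---|---|
| 2% | 30.6 | 31.0 |
| 5% | 31.6 | 32.6 |
| 10% | 33.3 | 35.6 |

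**5. No true effect (both arms average 20%).** The same formula, with 20 in place of 50, gives the spurious difference in points.

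| f (assumed) | m = −20 | m = 0 | m = 20 | m = 40 |
|---|---|---|---|---|
| 5% | +2.1 | +1.1 | 0 | −1.1 |
| 10% | +4.4 | +2.2 | 0 | −2.2 |

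The sign depends wholly on how the excluded patients would have done relative to the rest of their arm.

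**The case against.** The strongest reply is that the rule aims at the right population: people who actually have a PFO. Under Illustration A, unconfirmed patients respond like controls. Leaving their counterparts in the control arm then does not move the control mean, and 30 points is the correct effect among true PFO patients; 27.0-28.5 is that effect diluted. If closure does nothing, the same assumption gives 20 against 20 and no spurious difference. This stands: the gap in Illustration A cannot be called demonstrated inflation. It does not rescue the rule, because the assumption that makes it harmless cannot be checked when controls are never examined.

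It is also fair that few patients may be affected. Contrast echo and a bubble study precede randomisation, so the unconfirmed share could be below 5%.

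Four stronger readings are tempting, and the documents do not support them:
- **That the rule biases the result towards closure.** The Background hypothesis, that PFO contributes to seizures, makes this plausible, but no data show how unconfirmed patients respond, and the sign can reverse.
- **That the rule empties the control arm, since no control has confirmation.** The wording presupposes a procedure and is more naturally read as applying to those who had one.
- **That the PPS mainly removes closure patients with procedural complications.** Serious adverse events include hospitalisation (Section 10.3), and Section 8 lists status epilepticus and seizures with cardiac arrest. These can occur in either arm, so the direction is unknown.
- **That the FAS is the stated primary set.** It is the conventional inference, but the protocol never says so.

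**Conclusion.** The FAS definition is wrong as written. It contradicts its own opening statement and allows exclusion after randomisation in one arm only. With the PPS defined as it is, neither efficacy set preserves the randomised comparison; the SS keeps everyone but serves safety. This conclusion rests on the text alone and needs no assumed rate.

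The size is unknown. Over assumed non-confirmation rates of 2-10%, with excluded patients averaging a 0-20% reduction and an all-randomised closure mean of 50%, the exclusion adds 0.6 to 5.6 points to the difference. On the alternative assumption that confirmed patients average 50% and unconfirmed patients 20%, the gap is 1.5 to 3.0 points at 5-10%, part or all of which may be a change of target population. These figures are small against a standard error of about 7 points. The case for correction is therefore the loss of the analysis as randomised, with a bias that cannot be measured from the trial's own data, and not a large expected distortion.

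**What to change.** - Define the FAS as all randomised participants, analysed in the arm to which they were assigned, and name it as the primary efficacy set.
- Delete the intracardiac echo exclusion, or keep it only as a supplementary analysis labelled as not comparing the randomised groups.
- If an analysis restricted to confirmed PFO is wanted, base it on the contrast echo or the baseline bubble study obtained before randomisation, with one criterion applied to both arms.
- Remove serious adverse events from the PPS exclusions. They are outcomes, not departures from the protocol.

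The cost is wording in the protocol and any analysis plan, settled before the data are analysed. The sample size stays at 88 evaluable and about 110 recruited, and no examination is added. The estimate may turn out less favourable to closure.
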